**Study Protocol**

1. **Study Population**

The study will include female patients diagnosed with benign ovarian tumors, uterine fibroids, or secondary infertility who are scheduled for laparoscopic diagnosis and treatment. Inclusion criteria: (1) Age between 18 and 59 years; (2) American Society of Anesthesiologists (ASA) physical status I–II; (3) Body Mass Index (BMI) between 18.5–28 kg/m². Exclusion criteria: (1) Patients with chronic pulmonary diseases, infections, or severe pulmonary complications such as acute respiratory failure; (2) History of thoracic or pulmonary surgery or alveolar disorders; (3) Severe cardiovascular, cerebrovascular, hepatic, renal, or neurological diseases affecting respiratory function; (4) Smoking history within 8 weeks prior to surgery. Elimination criteria: (1) Surgical time less than 1 hour or longer than 6 hours, or pneumoperitoneum time less than 2 hours; (2) Intraoperative conversion to open surgery.

1. **Sample Size**

This study adopts a randomized crossover design with a target enrollment of 50 patients. After accounting for signal loss and data interference during surgery, the final number of patients with valid EIT data is 50. No formal sample size calculation was performed; the study is exploratory in nature.

1. **Group Allocation and Experimental Process**

A randomized crossover design will be used. The perioperative period is divided into five phases: pre-anesthesia (AWAKE), post-induction (BEGIN), first surgical phase (MIDDLE-1), second surgical phase (MIDDLE-2), and pre-extubation (END). Each patient will undergo both VCV and PCV-VG ventilation modes in random sequence, with a 30-minute washout period between modes.

1. **Randomization and Blinding**
2. **Randomization:** A random sequence will be generated using SAS software. Patients will be assigned to either the VCV-to-PCV-VG group or the PCV-VG-to-VCV group based on allocation order.
3. **Blinding:** This is an open-label study due to the need for real-time adjustment of ventilation by anesthesiologists. However, data analysis will be performed by an independent evaluator, and both patients and postoperative assessors will be blinded to group assignments.
4. **Anesthesia Protocol**

Patients will fast for 8 hours preoperatively. Upon entering the operating room, standard monitoring will be initiated (ECG, SpO₂, NIBP), and baseline vitals recorded. An epidural catheter will be placed at the L1-L2 interspace under local anesthesia. An EIT belt will be placed at the 4th–5th intercostal space, followed by radial arterial and central venous catheterization. All patients will receive 100% oxygen pre-oxygenation.
Anesthesia will be induced with remimazolam (0.3 mg/kg), sufentanil (0.3 µg/kg), cisatracurium (0.3 mg/kg), and propofol (2 mg/kg), followed by tracheal intubation and initiation of mechanical ventilation. Anesthesia will be maintained using combined intravenous and inhalational anesthesia, with intermittent epidural administration of 0.3% ropivacaine and sevoflurane inhalation. BIS will be maintained between 40–60. Fluid therapy and vasoactive drug use will be determined by the attending anesthesiologist to maintain hemodynamic stability. Intra-abdominal pressure during pneumoperitoneum will be set at 12 mmHg. At the end of surgery, anesthetics will be adjusted or withdrawn, and a standard epidural patient-controlled analgesia (PCA) pump will be connected. Patients will be transferred to the PACU after the recovery of spontaneous breathing.

1. **Ventilation Modes for EIT Monitoring**

EIT-1000 (Suzhou Jiantong Medical Technology, China) will be used for monitoring, with a recording frequency of 20 fps. All patients will have PEEP set to 5 cmH₂O, tidal volume to 7 mL/kg, I:E ratio at 1:2, FiO₂ maintained between 30% - 50%, and P_ET_CO₂ controlled within 35 ± 5 mmHg.
 In the VCV-to-PCV-VG group, patients will initially receive volume-controlled ventilation (VCV), followed by a switch to pressure-controlled volume guaranteed (PCV-VG) mode. In the PCV-VG-to-VCV group, the sequence is reversed.

1. **Outcome Measures**

(1) **Primary outcomes:**

- Electrical Impedance Tomography (EIT) parameters: center of ventilation (CoV), global inhomogeneity index (GI), and regional ventilation delay index (RVDI);
- Respiratory mechanics: plateau pressure (Pplat), driving pressure (∆P);
- Oxygenation index (PaO₂/FiO₂).

(2) **Secondary outcomes:**

- Hemodynamic parameters: mean arterial pressure (MAP), heart rate (HR), arterial carbon dioxide (PaCO₂);
- Regional EIT ventilation distribution (ROI 1–4);
- Dynamic lung compliance (Cdyn) during surgery.

1. **Statistical Analysis**

Data will be analyzed using SPSS 26.0. Continuous variables with normal distribution will be expressed as mean ± standard deviation and analyzed using paired t-tests. Non-normally distributed data will be presented as median (interquartile range) and analyzed using Wilcoxon signed-rank tests. Categorical variables will be compared using chi-square or Fisher’s exact tests. A p-value < 0.05 will be considered statistically significant.

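### PaO₂/FiO₂ is a primary outcome, but nothing holds FiO₂ equal between a patient's VCV and PCV-VG measurements

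*Protocol*

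**What the plan says.** Under *Outcome Measures*, the protocol names the "Oxygenation index", defined as PaO₂/FiO₂, as a primary outcome. It stands beside three EIT parameters and two pressures, so there are six primary variables.

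*Ventilation Modes for EIT Monitoring* gives single values for most settings: "All patients will have PEEP set to 5 cmH₂O, tidal volume to 7 mL/kg, I:E ratio at 1:2". FiO₂ is given only as a range, "maintained between 30% - 50" per cent.

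The comparison is within patients: "Each patient will undergo both VCV and PCV-VG ventilation modes in random sequence" (*Group Allocation and Experimental Process*). Normally distributed data are summarised as "mean ± standard deviation and analyzed using paired t-tests", with the Wilcoxon signed-rank test otherwise (*Statistical Analysis*).

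*Randomization and Blinding* states: "This is an open-label study due to the need for real-time adjustment of ventilation by anesthesiologists". The protocol does not say who sets FiO₂, when it may be changed, or that it must match between a patient's two mode periods.

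**The concern.** A crossover earns its efficiency by making each patient her own control. That works only if nothing but the mode differs systematically between her two measurements, and if incidental differences are kept small. FiO₂ is the denominator of this outcome and also drives its numerator. Because PaO₂ is not proportional to FiO₂, the ratio moves with FiO₂ even when the lung has not changed.

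Two consequences are possible. If FiO₂ changes between periods for reasons unrelated to mode, the paired difference becomes noisier. If it changes in relation to mode, for example because the anesthesiologist responds to saturation under one mode, the comparison is biased. Randomised order balances drift over surgical time but does not protect against a mode-related FiO₂ difference.

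FiO₂ is a bedside setting, so an analysis plan could not fully repair this. FiO₂ is set after randomisation and may respond to the mode itself. Adjusting for it, or dropping pairs with unequal FiO₂, could introduce bias.

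**Working it through.** The protocol gives no effect size, SD or power for this outcome, so there is no figure of its own to reproduce. That the holding rule is absent is settled by reading the text. The calculation below only sizes the consequence.

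**Inputs from the protocol:** FiO₂ 0.30 to 0.50; 50 patients; significance level 0.05 (taken as two-sided).

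**Assumed inputs:** barometric pressure 760 mmHg, PaCO₂ 40 mmHg, R 0.8, Hb 12 g/dL, arteriovenous O₂ difference 4.5 mL/dL, shunt fraction *s* as listed, background SD of the paired difference 40 mmHg.

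**Step 1: alveolar PO₂.** PAO₂ = FiO₂ × (760 − 47) − 40 × [FiO₂ + (1 − FiO₂)/0.8].

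- FiO₂ 0.30: 213.9 − 47.0 = 166.9
- FiO₂ 0.40: 285.2 − 46.0 = 239.2
- FiO₂ 0.50: 356.5 − 45.0 = 311.5

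Even with no shunt, PAO₂/FiO₂ rises from 556 to 598 to 623.

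**Step 2: arterial PO₂.** O₂ content is C(P) = 1.34 × 12 × S(P) + 0.0031 × P, with the Severinghaus curve S(P) = 1/[1 + 23400/(P³ + 150P)]. Arterial content is C(PAO₂) − 4.5 × s/(1 − s). Solving for PaO₂ and dividing by FiO₂ gives PaO₂/FiO₂ in mmHg:

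| Shunt | FiO₂ 0.30 | 0.40 | 0.50 | 0.30→0.40 | 0.30→0.50 |
|---|---|---|---|---|---|
| 5% | 417 | 440 | 480 | +23 | +63 |
| 10% | 331 | 318 | 341 | −13 | +10 |
| 15% | 277 | 245 | 240 | −32 | −37 |

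Over Hb 10 to 14 g/dL and O₂ difference 3.5 to 5.5 mL/dL, the 0.30→0.50 shift runs from about +47 to +75 at 5% shunt, −17 to +43 at 10%, and −54 to −7 at 15%. A dissolved-oxygen coefficient of 0.003 instead of 0.0031 gives central values of +60, +5 and −41.

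**Step 3: added noise, upper scenario.** Take the same lung in both periods, with FiO₂ drawn independently and equally often from 0.30, 0.40 and 0.50 in each. The added variance of the paired difference is then twice the variance of the three ratios. At 5% shunt the mean is 445.7 and the variance (821.8 + 32.1 + 1178.8)/3 = 677.6, so the added SD is √(2 × 677.6) = 36.8. The same sum gives 13.3 at 10% and 23.2 at 15%. Averaging the variance over a uniform spread of shunt gives an added SD of 35.5 (2–8%), 25.7 (3–15%) or 16.9 (8–15%).

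**Step 4: detectable difference** = 2.80 × SD/√50 (80% power, normal approximation).

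- No FiO₂ variation: SD 40, giving 15.8 mmHg
- Added SD 16.9: √(1600 + 285.6) = 43.4, giving 17.2
- Added SD 25.7: √(1600 + 660.5) = 47.5, giving 18.8
- Added SD 35.5: √(1600 + 1260.3) = 53.5, giving 21.2

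**Step 5: milder scenario.** Step 3 makes two-thirds of pairs unequal. If only 20% were, the added variance scales by 0.2/0.667 = 0.3. The added SD becomes 9.3 to 19.4 and the detectable difference 16.3 to 17.6 mmHg, a loss of about 3% to 11%.

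**Step 6: bias, if it occurred.** Suppose FiO₂ were 0.40 rather than 0.30 in 20 percentage points more of the periods in one mode than in the other. The mean difference would shift by 0.2 × 23 = 4.6 mmHg at 5% shunt, or 0.2 × (−32) = −6.4 at 15%.

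**The case against.** The strongest counter-case is about weight, since the text is not in dispute. The FiO₂ window is bounded and identical for both modes, order is randomised, and nothing in the protocol suggests that FiO₂ will differ by mode. The sentence on real-time adjustment explains the open label and does not mention FiO₂. The range may be meant to cover differences between patients, each then held steady. The larger shifts need a full swing from 0.30 to 0.50 in one patient, and the sign reverses with shunt. The physiology and the background SD are assumed, and an SD of 40 may already include some FiO₂ variation. The study calls itself exploratory, with no power target to miss, and the other five primary variables are not PaO₂/FiO₂ measures.

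Most of this stands as a limit on size: bias is possible rather than shown, and the realistic noise penalty is probably nearer Step 5 than Step 3. It does not close the gap. The reading that each patient is held at one value is reasonable, but the text does not secure it. An exploratory label does not make unmatched pairs comparable.

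**Conclusion.** The concern holds. The protocol standardises the other main ventilator settings at single values and leaves loose the one that enters a primary outcome directly. Under the assumed physiology, an FiO₂ change within the permitted range can move PaO₂/FiO₂ by tens of mmHg in either direction with no change in the lung. The likely practical effect is a modest loss of precision: a detectable difference of roughly 16 to 18 mmHg if a fifth of pairs are unequal, and up to about 21 under free variation, against 15.8 with FiO₂ held. Bias requires a mode-related FiO₂ difference, which the protocol does not prevent and gives no reason to expect. The absence of the rule is certain. The magnitudes are illustrative and rest on assumed shunt, haemoglobin, O₂ difference and SD. The change is worth making but does not threaten the study.

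**What to change.** In *Ventilation Modes for EIT Monitoring*, replace the FiO₂ range with a holding rule, for example:

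> FiO₂ is set to one value per patient within 30–50% (or 40% for all) before the first mode period and held unchanged in both mode periods through each blood gas. It is changed only for patient safety, and every change is recorded with time, mode and reason.

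With FiO₂ equal in both measurements, the artefact is zero by construction. Keep every pair in the main PaO₂/FiO₂ comparison, including those changed for safety. Report the number of unequal pairs by mode and examine them in a sensitivity analysis; these reporting details can sit in the analysis plan.

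The essential change is the rule to hold FiO₂ constant. It needs no extra patients or equipment, and costs only a little freedom to titrate FiO₂ around blood sampling.

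### If Cdyn is peak-pressure based and VCV runs at constant flow, the between-mode test of dynamic compliance leans towards PCV-VG even when the lung is unchanged

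*Protocol*

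**What the plan says.** All references are to the Protocol.

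- **Group Allocation and Experimental Process:** "Each patient will undergo both VCV and PCV-VG ventilation modes in random sequence", so the contrast is within patient.
- **Ventilation Modes for EIT Monitoring:** "All patients will have PEEP set to 5 cmH₂O, tidal volume to 7 mL/kg, I:E ratio at 1:2". These settings are common to both modes. No respiratory rate and no VCV flow waveform are given.
- **Outcome Measures:** "Dynamic lung compliance (Cdyn) during surgery" is secondary, without a formula. Plateau pressure and driving pressure are primary, without a statement of how plateau is read. Neither peak pressure nor airway resistance is listed.
- **Sample Size:** "a target enrollment of 50 patients", and "No formal sample size calculation was performed; the study is exploratory in nature".
- **Statistical Analysis:** normally distributed continuous variables are "analyzed using paired t-tests", others by Wilcoxon signed-rank test, with significance at p < 0.05. Nothing exempts Cdyn from this.

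**The concern.** Conventional dynamic compliance is VT/(Ppeak − PEEP). When VT and PEEP are held equal, it can differ between modes only through peak pressure. Under constant flow, peak pressure contains the resistive drop at full inspiratory flow. Under a pressure-controlled breath, flow decays during inspiration and much of that drop is gone by the end. The two modes can therefore give different Cdyn values for the same lung.

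If the plan is followed as written, that difference is tested at p < 0.05 and reported under the name of lung compliance. A reader would take a significant result as better mechanics under PCV-VG, although part or all of it could come from the flow pattern. No choice of statistical test removes this, and no listed outcome isolates the resistive part.

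**Working it through.** The plan gives no Cdyn value and no sample size calculation, so there is no stated figure to reproduce. The check asks what an unchanged lung would show.

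**Inputs from the protocol:** equal VT (7 mL/kg), PEEP (5 cmH2O) and I:E (1:2) in both modes; 50 pairs; p < 0.05, taken as two-sided.

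**Assumptions:** Cdyn = VT/(Ppeak − PEEP); constant flow in VCV; constant inspiratory pressure in PCV-VG; a single-compartment lung with resistance R and compliance C; 14 breaths/min in both modes. Weight is taken as 60 kg, so VT = 7 × 60 = 420 mL; this cancels from the ratio.

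**Formulas**, with Ti = 60/14/3 = 1.43 s and x = Ti/(RC):

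- VCV: Ppeak − PEEP = VT/C + R·VT/Ti, so Cdyn = C/(1 + 1/x).
- PCV-VG: Ppeak − PEEP = VT/[C(1 − e^(−x))], so Cdyn = C(1 − e^(−x)).
- Ratio PCV-VG/VCV = (1 + 1/x)(1 − e^(−x)).

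**Direction.** The ratio exceeds 1 exactly when e^x > 1 + x, which is true for every x > 0. Under these premises no resistance, compliance or inspiratory time reverses it.

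**Size.**

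| R (cmH2O/L/s) | C (mL/cmH2O) | x | Cdyn VCV | Cdyn PCV-VG | Ratio | Gap |
|---|---|---|---|---|---|---|
| 5 | 30 | 9.52 | 27.1 | 30.0 | 1.105 | 2.8 |
| 10 | 40 | 3.57 | 31.2 | 38.9 | 1.244 | 7.6 |
| 15 | 50 | 1.90 | 32.8 | 42.6 | 1.298 | 9.8 |

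Over a wider grid (10–20 breaths/min, C 20–60, R 5–20) the ratio runs from 1.05 to 1.298. The latter is essentially the mathematical maximum when VCV has no end-inspiratory pause. A pause in VCV widens the gap: with R 10, C 40 and 15 breaths/min, the excess is 25.4% without a pause, 28.6% with a pause of 10% of Ti and 32.6% with 20%.

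**Chance that the artefact alone is significant.** Paired t-test, n = 50, noncentrality = (gap/SD of differences) × √50. The SD is assumed, because the protocol gives none.

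| Gap (mL/cmH2O) | SD 4 | SD 6 | SD 8 | SD 10 |
|---|---|---|---|---|
| 3 | 0.999 | 0.934 | 0.739 | 0.548 |
| 5 | >0.99 | >0.99 | 0.991 | 0.934 |
| 7 | >0.99 | >0.99 | >0.99 | 0.998 |

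A standardised paired difference of 0.40 is detected with 80% power. The smallest artefact on the wider grid (C 20, R 5, 10 breaths/min) is 20.0 − 19.05 = 0.95. Even at SD 4 that is 0.95/4 = 0.24 SD, below that threshold.

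**After the change.** In the same model VT/(Pplat − PEEP), with plateau at zero flow, equals C in both modes. The ratio is 1.00.

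**The case against.** The strongest reply is that the two premises fixing the direction are not in the protocol. It defines Cdyn by name only and gives no VCV waveform; a formula could properly sit in a statistical analysis plan that is not at hand. A decelerating waveform in VCV, or a Cdyn fitted by regression to the equation of motion, would shrink or remove the artefact. This stands, and it makes the point conditional. It does not dispose of it: peak-based Cdyn and constant-flow VCV are the conventional readings, and the separate listing of plateau and driving pressure supports reading dynamic compliance as peak-based.

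A reader might also infer stronger claims that the documents do not support:

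- **That a significant result is close to guaranteed.** The probability falls to 0.55 for a gap of 3 at SD 10. Small gaps are plausible because Study Population limits entry to ASA I–II and excludes chronic pulmonary disease and recent smoking.
- **That the comparison says nothing about the lung.** The paired difference is the artefact plus any real change; it is confounded, not empty.
- **That the same artefact favours PCV-VG in plateau and driving pressure.** The reading method is not stated, and unequal methods could bias either way. With R 10 and C 40, a VCV pause shows 420/40 = 10.5 cmH2O above PEEP, while an end-inspiratory PCV-VG display shows 420/38.9 = 10.8, which counts against PCV-VG.
- **That compliance is the trial's main question.** The protocol states no such objective, and the mechanics among its primary outcomes are plateau and driving pressure.

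**Conclusion.** The concern holds in conditional form. With peak-based Cdyn and constant-flow VCV, the planned paired test compares peak pressures and leans towards PCV-VG for an unchanged lung. The lean is about 10% to 30% in the main assumed range and 5% to 30% in the wider one. The direction follows from the two premises and the single-compartment model; the size also rests on assumed resistance, compliance and rate. With 50 pairs, significance from the artefact alone is likely but not certain, and a real change in mechanics could not be separated from it.

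The consequence is limited. Cdyn is secondary, the study calls itself exploratory, and plateau and driving pressure are already primary. The plan should still be changed, because as it stands a flow-pattern difference could be reported as a gain in lung compliance.

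**What to change.** 1. Take peak-based Cdyn out of the between-mode significance test and report it as a within-mode descriptive figure. State its formula and the VCV flow waveform, and say that a between-mode difference reflects flow pattern and is not evidence of better lung compliance.
2. Rest between-mode mechanics on plateau pressure and driving pressure, and state that both are read under the same zero-flow condition in each mode.
3. If a compliance figure is wanted, show VT/(Pplat − PEEP) and label it a re-expression of driving pressure. With VT and PEEP fixed it is not separate evidence.

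**Cost:** one secondary between-mode test is lost. The rest is wording, unless an equal zero-flow reading is not already taken; in that case a brief end-inspiratory hold may be needed at each reading, which is a small procedural change.

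### The planned paired tests ignore period in a two-sequence crossover: any period effect is counted as error, and a chance imbalance between sequences goes uncorrected

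*Protocol*

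**What the plan says.** The design is a two-sequence, two-period crossover. Group Allocation and Experimental Process states: "Each patient will undergo both VCV and PCV-VG ventilation modes in random sequence, with a 30-minute washout period between modes". Randomization and Blinding adds: "Patients will be assigned to either the VCV-to-PCV-VG group or the PCV-VG-to-VCV group based on allocation order". Under Ventilation Modes for EIT Monitoring, in the first sequence "patients will initially receive volume-controlled ventilation (VCV), followed by a switch to pressure-controlled volume guaranteed (PCV-VG) mode"; the other sequence is the reverse. The second mode is therefore later in the operation for every patient, and the sequence decides which mode that is.

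Statistical Analysis fixes the tests for all continuous outcomes: "Continuous variables with normal distribution will be expressed as mean ± standard deviation and analyzed using paired t-tests". The alternative is: "Non-normally distributed data will be presented as median (interquartile range) and analyzed using Wilcoxon signed-rank tests". The decision rule is: "A p-value < 0.05 will be considered statistically significant". The protocol contains no period or sequence term. Sample Size gives 50 patients without a calculation and calls the study exploratory. Study Population lists eliminations that become known only during surgery (its duration, the duration of pneumoperitoneum, conversion to open surgery).

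**The concern.** A paired test on VCV minus PCV-VG pools the two sequences as if order did not matter. The two measurements are taken at different stages of one operation, with a 30-minute washout between the modes. A drift over time in ventilation distribution, pressures or oxygenation is plausible, though the protocol neither states nor quantifies one.

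A drift acts on the paired difference with opposite sign in the two sequences. This has two consequences. First, the spread between the sequences is counted as random error, so the mode effect looks less certain than it is. Second, if the sequences are unequal in size, the drift does not cancel, and part of it is reported as a mode effect. The randomised order makes both correctable, but the planned tests do not use it. This affects the main test of every continuous outcome, including all the primary ones.

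**Working it through.** **Inputs.** From the protocol: N = 50, two sequences, paired t or signed-rank test, significance at 0.05. Assumed: two-sided testing; a period shift π of 0.25, 0.5 or 1.0; splits of 25/25, 28/22, 30/20 and 32/18; a reference mode effect τ = 0.404, which gives the paired test 80% power when π = 0. All effects are in units of σ, the within-sequence SD of the patient's mode difference. The protocol has no power figure to reproduce.

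**Model.** Let d = VCV − PCV-VG and π = period 2 minus period 1. The mean of d is τ − π in the VCV-first sequence (n1 patients) and τ + π in the other (n2 patients).

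**Paired test.**
- Bias given the split: −π(n1 − n2)/N. Its size is 0 at 25/25, 6/50 = 0.12π at 28/22, 10/50 = 0.20π at 30/20 and 14/50 = 0.28π at 32/18.
- Inflation of the estimated standard error: about √(1 + 4·n1·n2·π²/N²). At 25/25 this is √(1 + π²), or 1.03, 1.12 and 1.41.

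**Period-adjusted test.** The estimate is the average of the two sequence means of d, in which π cancels for any split. Its standard error is (s/2)·√(1/n1 + 1/n2) on 48 degrees of freedom, where s is the pooled within-sequence SD.

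**Simulated type I error of the paired t-test, given the split** (at least 40,000 trials per cell; runs agree to within a few tenths of a point):

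| Split | π = 0.25 | π = 0.5 | π = 1.0 |
|---|---|---|---|
| 25/25 | 4.3% | 2.9% | 0.6% |
| 28/22 | 4.7% | 4.2% | 2.7% |
| 30/20 | 5.6% | 7.1% | 8.8% |
| 32/18 | 6.9% | 11.5% | 21 to 22% |

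**Power of the paired t-test at 25/25:** about 78%, 73% and 51%, against 80% with no period shift. At 28/22, when the bias opposes the effect, it is about 58% at π = 0.5 and 21% at π = 1.0, against 79% adjusted. If the bias runs with the effect, the rejection rate is raised instead, and so is the estimate.

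**Adjusted test:** type I error near 5% and power 76 to 80% in all these cases.

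**Signed-rank test:** it behaves alike. Its type I error is 4.1%, 3.0% and 0.5% at 25/25, and 6.6%, 11.4% and 21.1% at 32/18.

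**How likely the splits are.** Under simple 1:1 randomisation of 50, a split at least as unequal as 28/22 has probability 48%, 30/20 20% and 32/18 6.5%. Averaged over all splits, the paired test's type I error is 4.9 to 5.1% at every π considered. Each patient's order is then a coin toss, so d has mean τ and the shift only adds variance (σ² + π² in place of σ²).

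**The case against.** A reader might infer that the planned test inflates type I error, up to 22%. The protocol does not support that as a property of the plan. Under simple randomisation the paired test is unbiased and holds its level overall; with near-equal sequences it is conservative. The excess appears only given a marked imbalance together with a period shift. Conditioning on the observed split is legitimate, since the split is known at analysis, but 22% needs both a 32/18 split and a shift of a full SD. The eliminations could unbalance the sequences, but nothing in the protocol suggests that they depend on ventilation order.

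The size of the period effect is wholly assumed. PEEP, tidal volume and intra-abdominal pressure are set to common values, which may limit drift. At π = 0 the paired test is valid, and at π = 0.25 with equal sequences the loss is about two points of power. The 80% reference is mine, so no planned power is broken.

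Three further inferences should not be drawn. The protocol does not assign the first and second mode to MIDDLE-1 and MIDDLE-2; the argument needs only that one follows the other. It does not say on which quantity normality is judged, so a fault there is not shown. Its silence on blocking and confidence intervals may be detail left to an unseen SAP.

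What stands is that the protocol itself names tests without a period term for a design that randomises order. The exploratory label does not remove this, because the 0.05 rule is still applied and an exploratory estimate also benefits from precision.

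**Conclusion.** The point holds in a limited form and should be fixed before analysis. The planned tests are inefficient for this design whenever there is a period effect, and they leave a chance imbalance between sequences uncorrected. The main systematic harm is lost precision and power: at 25/25, from negligible at a shift of 0.25 SD to about 29 points (80% to 51%) at 1.0 SD. Bias and excess false positives are conditional on the split. They are absent at 25/25; at 28/22 there is bias but no excess type I error; both matter from about 30/20 onwards. These sizes rest on the assumed shifts, the assumed splits, normal differences with equal variance in the two sequences, and no carryover. The direction of the error does not depend on the assumed sizes.

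**What to change.** In Statistical Analysis, replace the paired t-test with a period-adjusted crossover analysis. Either of these will do:

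- a mixed model with fixed effects for mode, period and sequence and a random patient effect;
- a two-sample t-test comparing the within-patient period differences (period 1 minus period 2) between the two sequences, where half the difference in means estimates the mode effect.

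Replace the signed-rank test with a rank-sum test on the same period differences between the sequences.

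The cost is one degree of freedom (49 to 48) and a change of wording. If there is in fact no period effect and the split is unequal, a few points of power are lost: at τ = 0.4 and 32/18, about 75% against 79% for the paired test. At 25/25 there is practically no loss. The planned software can fit either analysis, and no new data are needed.

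### The choice between paired t-test and Wilcoxon is tied to normality of the measured variable, although in this crossover both tests act on the within-patient difference (minor)

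*Protocol*

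**What the plan says.** Under Statistical Analysis the protocol gives a two-branch rule. The first branch reads: "Continuous variables with normal distribution will be expressed as mean ± standard deviation and analyzed using paired t-tests". The second branch, worded for data and not for variables, prescribes a median with IQR and the Wilcoxon signed-rank test when normality fails.

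The significance level follows: "A p-value < 0.05 will be considered statistically significant". No test or plot for judging normality is named, and the within-patient difference appears nowhere in the document.

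The data are paired by design. Group Allocation and Experimental Process states: "Each patient will undergo both VCV and PCV-VG ventilation modes in random sequence". Sample Size gives a "target enrollment of 50 patients" and adds: "No formal sample size calculation was performed; the study is exploratory in nature".

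The rule applies to all six primary outcomes listed under Outcome Measures: three EIT parameters (CoV, GI, RVDI), two pressures (Pplat, ∆P) and PaO₂/FiO₂.

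**The concern.** A paired t-test is a one-sample t-test on the differences, so its distributional assumption concerns the differences. The signed-rank test, used as a test of location, relies on their symmetry. Normality of the values under each mode is neither necessary nor sufficient for either.

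The protocol ties the test to the same judgement that selects mean ± SD or median with IQR. Those summaries describe the variable, so the natural reading is that the variable is what gets judged.

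Two misassignments can follow:

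- **Normal-looking values, heavy-tailed differences.** The rule keeps the t-test, which is the more fragile choice here.
- **Skewed values, near-normal differences.** The rule moves to Wilcoxon without need.

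What is at stake is power to detect a difference between modes, in a study with 50 patients and no sample size calculation.

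**Working it through.** The protocol states no power figure, so there is none to reproduce.

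**Inputs from the protocol:** 50 pairs; significance level 0.05 (two-sided assumed); paired t-test or Wilcoxon according to normality.

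**Assumed, because the protocol gives no figures:** effect size, within-patient correlation ρ, outlier frequency and size, and Shapiro-Wilk at 5% as the normality check. The rule as written is taken to use the t-test only if the values under both modes pass. The corrected rule applies the same check to the differences.

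**Reference effect.** For 80% power with normal differences, the normal approximation gives (1.960 + 0.842)/√50 = 0.396 SD of the differences. The simulations use 0.40 or 0.404.

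**Why raw values hide the differences.** Write each reading as patient level plus error. The error share of the raw variance is 1 − ρ: 10% at ρ = 0.9, 20% at 0.8, 30% at 0.7 and 50% at 0.5. The patient level cancels in the difference, which apart from the mode effect is all error. The higher ρ is, the less an outlying error shows in the raw values.

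**Model A: outliers on single readings.** Each reading has probability p of a four-fold error SD; true effect 0.404 SD of the clean differences. At p = 10%, the share of pairs with at least one affected reading is 1 − 0.9² = 19%, or about 9 to 10 of 50.

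At ρ = 0.9 and p = 10%, the raw values pass in both modes in 81% of simulated trials, but the differences pass in only 30%. Power is about 50% under the written rule and 59% under the rule on differences, a loss of about 9 points. Repeat runs move both powers together by two or three points and leave the gap much the same.

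| ρ | Outlying readings | Power lost by the written rule |
|---|---|---|
| 0.8–0.9 | 5–10% | about 5 to 9 points (single runs start at about 4) |
| 0.8–0.9 | 1–2% | about 2 to 3 points |
| 0.7 | up to 10% | up to about 3 points |
| 0.5 | 0–10% | under 1 point |
| any | none | 2 points or less |

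**Model B: outliers on the differences themselves.** Core SD of the differences 1, shift 0.4, 6,000 runs per scenario. Between-patient SD is 3 or 2, which implies a core correlation of (9 − 0.25)/(9 + 0.25) = 0.95 or (4 − 0.25)/(4 + 0.25) = 0.88.

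| Differences | Rule on variable | Rule on difference | Loss (points) |
|---|---|---|---|
| 5% at 5 × SD | 57.0% | 71.5% | 14.5 |
| 10% at 5 × SD | 43.8% | 64.2% | 20.4 |
| 10% at 3 × SD | 57.2% | 66.2% | 9.0 |
| t with 3 df | 46.1% | 57.0% | 10.9 |
| normal, variable skewed | 76.9% | 78.8% | 1.9 |
| normal, variable normal | 78.6% | 78.6% | 0.0 |

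In the first four rows the written rule picks the t-test in about 89 to 91% of runs and the rule on differences in about 13 to 44%. In the skewed-variable row the two rules disagree in about 95% of runs, yet the loss is only about 2 points. Model B is the harsher set of assumptions, so the conclusion rests on Model A.

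**False positives.** With no true effect, the written rule rejects in 4.1 to 5.3% of runs across the Model B scenarios, so the nominal 5% level holds.

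**The case against.** The strongest reply is that this is stock wording. It names the correct paired tests, specifies no check, and in the Wilcoxon sentence refers to data, which could mean differences. This stands in part: the protocol does not state the procedure simulated here. But the t-test sentence speaks of variables and links them to a summary statistic of the variable. Even on the kinder reading, the same clarification is needed.

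It is also fair to say that the loss is material only when high correlation and frequent outliers coincide. In the worst Model A case the artefact itself takes power from 80% to 59%, and the rule takes a further 9 points, the smaller part. The study calls itself exploratory and claims no power, so no stated operating characteristic is contradicted. All of this stands and limits the severity.

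Four stronger readings are tempting but not supported:

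- **That the protocol expects artefact in the analysed data.** The words "After accounting for signal loss and data interference during surgery" introduce a count of 50 patients with valid EIT data. They describe interference as already dealt with, and they concern only the three EIT primary outcomes. Any remaining artefact is an assumption.
- **That false-positive conclusions are inflated.** The simulated rates do not show this.
- **That the categorical tests ignore the pairing.** The protocol says "Categorical variables will be compared using chi-square or Fisher’s exact tests", but lists no categorical outcome to compare between modes. Those tests suit comparisons of the two sequence groups.
- **That the test is left open when the two modes differ in shape.** How such a case is resolved is detail that a statistical analysis plan may hold.

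**Conclusion.** The point holds as a minor one. The protocol states a rule for choosing between two paired tests and keys it to the variable, when the quantity that matters is the within-patient difference. This is a problem of efficiency and not of validity.

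With 50 pairs the cost is about 5 to 9 power points if within-patient correlation is 0.8 to 0.9 and 5 to 10% of readings are outlying with four-fold error SD. It is about 3 points at correlation 0.7, and about 2 or less when the differences are near normal or the correlation is about 0.5. These sizes rest on assumed correlations, outlier patterns, effect size and normality check, none of which the document supplies. That the rule looks at the wrong quantity does not depend on them.

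**What to change.** Amend Statistical Analysis in one of two ways:

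1. State that the distribution is judged on the within-patient difference between VCV and PCV-VG, and that this judgement decides between the paired t-test and the Wilcoxon signed-rank test; or
2. Name one paired test for each primary outcome in advance and report the other as a sensitivity analysis. This removes the need for a data-driven normality rule.

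Either way, separate the summary statistic from the test: mean ± SD or median (IQR) can follow the shape of the values in each mode without deciding how the modes are compared.

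The cost is one or two sentences, with no new data and no additional patients.
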